# A study protocol for a multicenter randomized pilot trial of a dyadic, tailored, web-based, psychosocial, and physical activity self-management program (*TEMPO*) for men with prostate cancer and their caregivers

**DOI:** 10.1186/s40814-021-00791-6

**Published:** 2021-03-20

**Keywords:** Prostate cancer, Cancer survivorship, Cancer rehabilitation, Self-management, Caregivers, Dyadic intervention

## Abstract

**Background:**

Prostate cancer predisposes patients and caregivers to a wide range of complex physical and psychosocial challenges, and interventions must incorporate a wide range of self-management strategies to help patients and their caregivers effectively cope with cancer challenges. To palliate this need, our team recently developed and evaluated the initial acceptability of a dyadic, Tailored, wEb-based, psychosocial, and physical activity self-Management PrOgram (*TEMPO*). *TEMPO* is a 10-week, interactive, web-based intervention consisting of five modules designed to help dyads manage their physical and psychosocial needs. It aims to teach dyads new self-management strategies and encourages them to increase their physical activity (PA) levels, mainly through walking and strength-based exercises. Initial acceptability evaluation of *TEMPO* revealed high user satisfaction, in addition to having a number of potential benefits for participants. After integrating suggested changes to *TEMPO*, the proposed pilot study aims to further test the acceptability and feasibility of *TEMPO*.

**Methods:**

This study is a multicenter, stratified, parallel, two-group, pilot randomized control trial (RCT), where patient–caregiver dyads are randomized (stratified by anxiety level) to receive (a) *TEMPO* or (b) usual care. Participants (*n* goal = 40) are recruited across Canada at participating cancer centers and through self-referral (e.g., online recruitment). Patient inclusion criteria are (a) having received prostate cancer treatment within the past 2 years or scheduled to receive treatment, (b) identified a primary caregiver willing to participate in the study, and (c) has access to the Internet. Eligible caregivers are those identified by the patient as his primary source of support. Dyads complete a baseline questionnaire (T1) and another one 3 months later (T2) assessing various aspects of physical and emotional functioning (e.g., the Medical Outcomes Study (MOS) 12-item Short Form Health Survey (SF-12), the Hospital Anxiety and Depression Scale (HADS), and the Perceived Stress Scale (PSS)), self-management behaviors (e.g., the Health Education Impact Questionnaire (heiQ)), physical activity (the International Physical Activity Questionnaires (IPAQ) and the Multidimensional Self-efficacy for Exercise Scale (MSES)), and dyadic coping (the Dyadic Coping Inventory (DCI)). Dyads that used *TEMPO* are also asked to participate in a semi-structured exit interview exploring their overall experience with the program.

**Discussion:**

This feasibility analysis will begin to develop the knowledge base on *TEMPO*’s value for men with prostate cancer and their caregivers to inform a larger trial.

**Trial registration:**

NCT04304196

**Supplementary Information:**

The online version contains supplementary material available at 10.1186/s40814-021-00791-6.

## Introduction

### Background

Prostate cancer management presents patients and their caregivers with a myriad of complex physical and psychosocial challenges [1–3]. Informal caregivers (most often patients’ partners) help to alleviate the demands on the healthcare system [4], and contribute positively to patients’ illness adjustment [2, 3]. However, caregivers’ extensive support often results in high levels of physical, emotional, and social burden. A recent longitudinal analysis highlighted that 53% of caregivers report chronically poor physical functioning, and an additional 17% experience a steep decline in physical health over the first 5 years of providing care for a newly diagnosed person with cancer [5]. Likewise, the incidence of clinically significant levels of anxiety and depression among prostate cancer caregivers supersedes those of the patient [6], and these symptoms may persist for up to 5 years [7]. As such**,** 16 to 68% of caregivers report needing more support [3], particularly in curtailing the emotional and psychological impacts of cancer, and help looking after their own health.

A number of interventions have been developed to address caregivers’ unmet supportive care needs and enhance their quality of life (QOL) [8–10]. Most of these interventions are grounded in the principles of psycho-education and self-management to effectively address caregivers’ psychosocial and emotional needs [8, 9, 11], but fail to incorporate strategies to enhance caregivers’ physical well-being. As such, emerging literature [12, 13] has focused on incorporating regular physical activity (PA) into self-management interventions as a strategy to curtail the negative physical and emotional sequela associated with cancer caregiving. In line with this, in a survey on cancer caregivers’ preferences for stress-management strategies, nearly 75% of respondents stated that they were most interested in programs with an exercise component to reduce burden [12].

In recent years, two systematic reviews [13, 14] have collectively identified 17 PA interventions for family caregivers. Findings from these reviews provide preliminary evidence for the efficacy of PA interventions on caregivers’ psychosocial outcomes, notably in reducing distress, and increasing well-being, QOL, and self-efficacy [13]. However, only three [15–17] of the 17 interventions were developed for cancer caregivers. Martin and colleagues [16] designed a 6-week, group-based yoga intervention for caregivers of cancer survivors, whereas the other two interventions utilized a dyadic approach to engage breast [15] or lung [17] cancer patients and their partners in a 6-week low-intensity walking or yoga program, respectively. These dyadic PA interventions were found to lead to a significant decrease in anxiety and depressive symptoms for both members of the dyad, in addition to providing individual benefits (e.g., decreased sleep disturbances among caregivers) [15, 17]. These systematic reviews [13, 14] identified a need for more rigorous trials to support this approach in improving cancer caregivers’ outcomes. This is in line with studies suggesting that coordinating coping effort within the patient–caregiver dyad, such as engaging in PA together, can contribute significantly to both the patients’ and caregivers’ well-being [18, 19]. Dyadic PA interventions conducted with non-cancer caregivers have also been found to be efficacious [13].

Since the aforementioned caregiver PA intervention reviews have been published [13, 14], the RECHARGE dyadic PA intervention for cancer dyads has been developed and aims to capitalize on the opportunity to enhance both patient and caregiver outcomes [20]. RECHARGE is a 12-week exercise intervention aimed at caregivers providing physical or psychological support to a patient with any type of cancer. It is a structured healthcare provider (HCP)-facilitated intervention consisting of: two weekly group-based resistance exercise sessions, 7 group-based education sessions, and individual weekly aerobic exercise sessions [20]. Although RECHARGE has also been found to be efficacious at improving a number of psychosocial outcomes among dyads [20], the literature suggests that structured HCP-driven interventions may not be sustainable in the long run due to their high cost and lack of flexibility [11]. As such, there is a need to find alternate delivery formats (e.g., self-directed or home-based formats) that provide ongoing instructions and support in a way that is cost-effective and that offer participants the flexibility to choose when and where to engage in the program [21, 22].

Two dyadic cancer interventions for patients and caregivers (FOCUS [23] and CARES [24]) exist in a self-administered web-based format; however, neither incorporates PA self-management strategies. Nonetheless, these studies provide evidence that this approach to program delivery is efficacious in reducing emotional distress and improving QOL and self-efficacy [23, 24]. A recent systematic review [25] of online exercise-based interventions for breast cancer patients (but not their caregivers) found that participant adherence to these programs was generally high. Moreover, participants rated the interventions as acceptable and beneficial, particularly if they assessed them to offer tailored content in a time- and cost-effective manner [25]. Taken together, these studies [20, 23–25] have laid important groundwork for the development of the first dyadic, Tailored, wEb-based, psychosocial and PA self-Management PrOgram (*TEMPO*) for men with prostate cancer and their caregivers.

Our team recently concluded a qualitative study evaluating the acceptability and usefulness of *TEMPO* to facilitate patient–caregiver dyads’ access to QOL-enhancing support and information, tailored to their needs [26]. The findings of this study emphasized that cancer patients and their caregiving partners were satisfied with both *TEMPO*’s dyadic approach (e.g., joint goal setting to integrate self-management skills to cancer care) and the extensive informal support it provided. A number of preliminary benefits were described, notably in the domains of physical well-being (e.g., increased PA and improved overall health), emotional support (e.g., reduced anxiety and improved stress management), psychosocial support (e.g., improved communication, increased teamwork, supported goal fulfillment), and informational support (e.g., increased knowledge and repertoire of self-management skills). Following this initial acceptability study, changes were made to *TEMPO*, including adjustments to imagery and language, improvements to navigation and flow, and finalizing the French version.

### Aims and objectives

The primary aim of this pilot trial is to further test the acceptability and feasibility of *TEMPO*. A secondary aim is to examine the clinical significance of *TEMPO*.

The objectives are to
Examine the acceptability of *TEMPO*, including satisfaction, adherence, perceived usefulness, and attrition [27]Examine feasibility defined as rates of recruitment, retention, and questionnaire completion [27]Estimate the clinical significance on anxiety and QOL (primary outcomes), as well as depression, self-management skills, PA, self-efficacy, and appraisal (secondary outcomes)

### Pilot outcomes justifying a larger trial

As a pilot is not suitable for hypothesis testing [28], the focus is on pilot outcomes justifying a larger trial. Given the lack of published benchmarks for feasibility and acceptability, we aim to introduce rigor by nominating the following values:
The pilot procedures will be feasible if (a) eight dyads/month are recruited across sites, (b) refusal rate does not exceed 45%, (c) missing data are less than 10% [29], and (d) protocol infringements are amenable to change.*TEMPO* will be acceptable if (a) attrition in the intervention group does not exceed 25% [30, 31], (b) 75% of dyads adhere to the *TEMPO* modules, and (c) high system usability is reported.An appropriate measure of clinical significance for a pilot is the effect size (ES) [CONSORT for pilots [28]]. A clinically (not statistically) meaningful finding is defined as an ES > 0.2 [32] for the primary outcomes (QOL and anxiety) of interest at 3 months post-baseline compared with those in the control group. As a secondary assessment of clinical significance is that 25% of participants improve on the primary outcomes by at the least the Minimal Clinically Important Difference (MCID).

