#### Medical Outcomes Study (MOS) 12-item Short Form Health Survey (SF-12) [57]

The SF-12 yields a Physical Component Summary (PCS) and a Mental Component Summary (MCS) score [57]. This scale has been used in other caregiver studies [5, 58, 59]. The scores are calculated using weighted scoring and standardized from 0–100 (US norm mean = 50, SD = 10). Internal consistency of the SF-12 PCS (α = 0.82) and MCS (α = 0.75) have been assessed to be adequate [60] across nine European countries including France [61].

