#### Clinical significance

An intention-to-treat analysis will be conducted and missing data will be accounted for via multiple imputation. Baseline imbalances across intervention and control groups will be examined for each outcome score. As this is a pilot trial, effect sizes to estimate the clinical significance of the interventions will be calculated by computing differences between two estimated means divided by the pooled standard deviation [32]. In addition, the proportion of participants that improved on the primary outcome measures by at least the minimal clinically important difference (MCID) will be calculated. The MCID for patients with cancer and their caregivers for the HADS and SF-12 are not available; however, validated MCIDs in other populations will be used. For the HADS, the MCID that will be used is 1.5 [87] and for the SF-12 MCS 3.8 [88] and PCS 3.3 [88]. Subsequent inferential statistics will be carried out for exploratory purposes only to inform the planning of the larger trial. In the event that groups are imbalanced at baseline, they will be compared using regression analysis where the baseline scores will be included in the model as a covariate. No corrections will be undertaken for multiple testing due to the exploratory nature of this pilot.

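### The secondary criterion that 25% of participants improve by the MCID has no control comparison, and on either SF-12 score alone measurement error can reach that level.

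*Protocol article*

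**What the plan says.** The protocol article, under 'Pilot outcomes justifying a larger trial', gives two measures of clinical significance. The leading one is an effect size above 0.2 on QOL and anxiety, "at 3 months post-baseline compared with those in the control group". The next sentence adds a secondary assessment: "25% of participants improve on the primary outcomes by at the least the Minimal Clinically Important Difference". That sentence states no arm, no comparator and no basis for 25%.

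Under 'Data analysis', 'Clinical significance', the article says only that "the proportion of participants that improved on the primary outcome measures by at least the minimal clinically important difference (MCID) will be calculated". The thresholds follow: for the HADS "the MCID that will be used is 1.5 [87] and for the SF-12 MCS 3.8 [88] and PCS 3.3 [88". They are borrowed, since "validated MCIDs in other populations will be used".

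The SF-12 section supplies the scale's spread, "US norm mean = 50, SD = 10", and its reliability: "Internal consistency of the SF-12 PCS (α = 0.82) and MCS (α = 0.75) have been assessed to be adequate". The HADS section gives alphas of 0.68–0.93 overall and 0.79–0.89 for the French Canadian version, but no SD. The target at three months is 20 dyads per group, that is 40 individuals per arm. Control dyads complete the same outcome measures at baseline and at three months.

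**The concern.** A proportion of improvers has a meaning for TEMPO only against the proportion that would improve without it. Scores measured with error move between two occasions even when the person has not changed, and some of those movements exceed the MCID in the favourable direction. If that background rate is already near 25%, a programme with no effect can meet the criterion. The result would then appear among the grounds for a larger trial although it says nothing about TEMPO. The trial is randomised and collects what is needed for the comparison, so the weakness lies in how the criterion is worded.

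**Working it through.** The 25% is a nominated value with no derivation, so there is no figure to reproduce. The check is what proportion would improve by the MCID if nobody truly changed.

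**Inputs from the article.** SF-12 SD 10; alpha 0.75 (MCS) and 0.82 (PCS); MCIDs 3.8 (MCS), 3.3 (PCS) and 1.5 (HADS); HADS alpha 0.68–0.93; 40 individuals per arm.

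**Assumptions.** Alpha stands in for three-month retest reliability. Errors are normal. The SF-12 SD in this sample may lie between 8 and 12. The HADS-Anxiety SD, which the article does not give, may lie between 3 and 5. Individuals are treated as independent, ignoring dyads.

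**Formulas.** SD of change = SD × √(2 × (1 − reliability)). Noise rate = 1 − Φ(MCID / SD of change). Chance that an inert arm passes = P(X ≥ 10) for X binomial with n = 40 and p = noise rate.

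**SF-12 at SD 10**
- MCS: SD of change = 10 × √0.50 = 7.07; 3.8/7.07 = 0.537; noise rate 29.5%; chance of passing 79%.
- PCS: SD of change = 10 × √0.36 = 6.00; 3.3/6.00 = 0.550; noise rate 29.1%; chance of passing 77%.

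**SF-12 over the assumed SD range**

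| SD | MCS noise rate | MCS pass | PCS noise rate | PCS pass |
|---|---|---|---|---|
| 8 | 25.1% | 57% | 24.6% | 54% |
| 10 | 29.5% | 79% | 29.1% | 77% |
| 12 | 32.7% | 89% | 32.3% | 88% |

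At SD 10, reliability would have to exceed 0.84 (MCS) or 0.88 (PCS) for noise to fall below 25%. The alphas quoted are lower.

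**HADS-Anxiety noise rate, MCID 1.5**

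| Reliability | SD 3 | SD 4 | SD 5 |
|---|---|---|---|
| 0.68 | 27% | 32% | 35% |
| 0.80 | 21% | 28% | 32% |
| 0.93 | 9% | 16% | 21% |

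Whole-number scoring with a floor at 0 and a ceiling at 21, checked by simulation at SD 3–4, changes these by about one point or less. The rate falls on either side of 25%.

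**Effect of the any/each/all ambiguity** (errors independent across outcomes, SF-12 SD 10, HADS SD 4, reliability 0.80)
- A person counts if any one outcome improves: noise rate 1 − (0.723 × 0.705 × 0.709) = about 64%.
- Each outcome must separately reach 25% in the arm: 0.79 × 0.77 × 0.70 = about 43% chance of passing. Over the HADS ranges above this runs from under 1% to about 57%.
- The same person must improve on all three: noise rate 0.277 × 0.295 × 0.291 = about 2%, far below 25%.

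**With a control contrast.** An inert programme has an expected between-arm difference of zero, whatever the noise rate. At about 29.5% in each arm of 40, the 95% CI half-width is 1.96 × √(2 × 0.295 × 0.705 / 40) = 0.20, or about ±20 percentage points. For patients or caregivers alone (20 per arm) it is 1.96 × √(2 × 0.295 × 0.705 / 20) = 0.28, or about ±28 points.

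**The case against.** The strongest reply is about weight. This is a secondary assessment within a secondary aim. The leading criterion, an effect size above 0.2, is explicitly against control, and feasibility and acceptability have their own criteria. The flaw cannot decide progression by itself. That stands, and it limits the severity.

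Second, a reader might infer that an inert programme would usually pass. The documents do not support that in general. It holds when one SF-12 score is judged alone, and at SD 8 the chance is only 54–57%. The criterion refers to primary outcomes in the plural. If each outcome must pass, the chance is often below one half, and if one person must improve on all, noise falls far short. For HADS-Anxiety the answer turns on an SD that the article does not give.

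Third, a reader might expect recovery, regression to the mean or easing of pandemic restrictions to push the rate higher. The article does not establish this. It also enrols patients still awaiting treatment, who may worsen. It does not select on high distress. It says that pandemic restrictions may shift scores in either direction. These influences are reasons to want a control comparison, but their net direction is unknown.

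Fourth, tabulation by arm may be set out in a fuller protocol or analysis plan. It may, but the article itself fixes the pass level, and an added table would not change a rule that contains no comparison.

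**Conclusion.** The concern holds at moderate severity. As written, the criterion cannot attribute improvement to TEMPO: it has no arm, no comparator and no any/each/all rule. On the article's own figures, measurement error alone gives about 29–30% improved on MCS or PCS taken singly, and about 25–33% over SD 8–12. An arm of 40 with no true change would reach 25% on one SF-12 score about 77–79% of the time, or 54–89% over that SD range. For HADS-Anxiety the noise rate of about 9–35% may lie above or below the bar.

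These sizes rest on alpha as a proxy for retest reliability, on the US norm SD applying here, and on ignoring within-dyad correlation. The absence of a control contrast rests on none of them. The effect-size criterion and the feasibility and acceptability criteria are untouched.

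**What to change.** For each of HADS-Anxiety, MCS and PCS, report the proportion improving by at least the MCID in each arm, separately for patients and caregivers. Give the TEMPO-minus-usual-care difference with its 95% CI, presented as estimation. State that outcomes are assessed one at a time, which removes the any/each/all ambiguity. Do not use the uncontrolled 25% level as evidence for a larger trial.

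The cost is analysis wording only, since the control arm already supplies the data. The downside is that the contrast is imprecise at this size (about ±20 points at 40 per arm, wider by role and with dyad correlation ignored). It is also likely to look less favourable than a single proportion. It therefore suits description rather than a new pass/fail rule, in line with the article's own position that a pilot is not for hypothesis testing.

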## Methods

### Design

The proposed study is a multicenter, stratified, 1:1, parallel, two-group pilot randomized control trial, whereby patient–caregiver dyads are randomized to receive (a) *TEMPO* or (b) usual care. At the conclusion of the pilot study, semi-structured exit interviews are conducted. The study design was guided by the CONSORT checklist [33] and its adaptation to pilot trials [28]. The reporting of this protocol is according to the SPIRIT guidelines [34]. Supplementary Material S1 includes both the CONSORT and SPIRIT checklists.

### Methodological framework

The *Complex Interventions Framework* [35] describes four steps in the development and evaluation of complex interventions: (a) development, (b) feasibility/pilot testing, (c) evaluation, and (d) implementation. This study focuses on (b).

### Sample and setting

A convenience sample of patients and their caregivers is being recruited (as a dyad) from the McGill University Health Centre (MUHC); St. Mary’s Hospital, an installation of the Montréal West Island Integrated University Health and Social Services Centre (SMHC); Tom Baker Cancer Centre (TBCC); Vancouver General Hospital (VGH); and Sunnybrook Health Sciences Centre (SHSC). Recruitment was initiated on April 2020 and concluded in February 2021. Patient inclusion criteria are (a) having received prostate cancer treatment (surgery, chemotherapy, radiation therapy, hormone therapy, and/or brachytherapy) within the past 2 years or scheduled to receive listed treatments, (b) identified a primary caregiver willing to participate in the study, and (c) has access to the internet.

Eligible caregivers are those identified by the patient as his primary source of support regardless of the type of support provided (emotional support, help with activities of daily living, etc.) and their relationship to the patient. Patients/dyads in the acute survivorship phase (within 2 years of active cancer treatments) are targeted, as this corresponds with a period of high distress for caregivers whereby support is needed to prevent chronic distress [36]. Further, caregivers of men with localized or advanced cancer, and spousal or family caregivers are primary targets for inclusion in the present study, as these caregiver subgroups have all been found to benefit from similar self-management interventions [37–39]. Caregivers who were diagnosed with cancer in the previous year, or who are currently receiving treatment for cancer are excluded. Patients and caregivers both need to be able to understand English or French due to the availability of the *TEMPO* platform in these languages.

